## **4.2.3. Nutritional Assessment (II, VI)**

### **Anthropometric measures (II,IV)**

Anthropometric measures will include weight, height and specific measures to determine body composition, namely a triceps skinfold thickness and medial calf skinfold thickness.

Weight will be measured to the nearest 0,1 kilogram and height will be measured to the nearest 0,5 centimeters. Subjects will be lightly clothed and bare-footed.

After height and weight, it will be calculated body mass index (BMI) - weight (kilograms) divided by square of height (meters).

Individuals will be classified according to World Health Organization (WHO) classifications: normal weight, 18.5 to 24.9 kg/m^2; overweight, 25.0 to 29.9 kg/m^2; obesity, 30.0 kg/m^2 or plus.

Skinfold thickness measurement will be taken using a slim guide skinfold calipers and according to procedures described by International Society for the Advancement of Kinanthropometry (ISAK)[49]. Three measurements will be taken, at each site (+/- 0,1 mm). Percentage body fat will be calculated using prediction equations (Males: % body fat = 0,735 \* (triceps + calf) + 1.0 / Females: % body fat = 0,610 \* (t+c) + 5.1), as previously published [50].

Waist circumference will be measured according to procedures described on ISAK[49]. Individuals will be classified in abdominal overweight or obese, according to the following sex-specific cut-offs: females - abdominal overweight 80 - 88 cm, abdominal obesity 88 cm or plus; males - abdominal overweight 94 - 102 cm, abdominal obesity 102 cm or plus[51].

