#### **4.2.4. Airway Inflammation (III)**

Sputum collection and analysis will be performed as described previously in literature [52]. Patients will perform previously bronchodilation with salbutamol followed by a protocol of inhalation of hypertonic saline (5%NaCl) generated by an ultrasonic nebulizer during 5 min periods for 20 min. Sputum will then be obtained. After the sample is collected it will be selected in a Petri dish, and the selected sample treated with dithiothreitol (Sputolysin; Calbiochem Corporation, San Diego, CA, USA). The suspension will be centrifuged and the cell pellet re-suspended. Cytospins will be prepared and stained using May-Grünwald/Giemsa. Differential cell counts will be made by counting a minimum of 500 nonsquamous cells. Sputum eosinophilia will be defined as a sputum differential of eosinophil count over 4%.

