### **4.3.2. Respiratory Infection susceptibility in athletes and elderly (II,III)**

All potential risk factors for respiratory infections will be analyzed for two different in risk populations, elderly and athletes (II,III). Elderly clinical trial will be analyzed as a completed-protocol (III).

Descriptive values for each risk factor will be calculated and Relative Risk to Respiratory Infection with the respective confidence intervals at 95% assessed.

Multiple linear regression and logistic regression models will be used as appropriate to modulate for possible confounders, namely respiratory infections and their severity will be given by questionnaire scores. Univariate and multiple logistic regression models will be developed using independent variables as risk factors for having respiratory tract infections. Results will be presented as odds ratio (OR) with [95% confidence interval (CI)].

Variables potentially included in the model for swimmers illness profile (II) will be: gender, age, BMI (variable categorized), anthropometric changes, history of respiratory tract disease, smoking habits, previous influenza immunization, probiotics consumption, vitamins consumption, sleep quality, anxiety, nutritional status, urinary metabolomic profile, asthma, bronchial hyper-responsiveness, airway inflammation presence and immunological mediators.

Variables used in the elderly intervention model will included: gender, age, BMI, history of respiratory tract disease, diabetes, smoking habits, previous influenza immunization and previous practiced exercise training.

Models will be performed by data driven and progressively adjusted considering its goodness-of-fit (assessed by Hosmer-Lemeshow test) and predictive power (evaluated by ROC curve analysis).

For the moderate exercise intervention trial in elderly (II) sample power was calculated as infrastructure conditions only allowed a maximum sample of 40 persons in each group to be included. Relative risk of having an infection in the training group and in control group will be used. In the previous published literature assessing postmenopausal women [24], having an infection during an moderate-exercise intervention, 48% had at least one episode of respiratory infections compared to control group, which had at 30% in the second. Assuming an alpha of 0.05 on exercise group had 48% change of having infection and 30% of having infections in the non-exercising group the power would be 30%.

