#### Sample size calculation

In the athletes population, all swimmers under competition in the Porto's team Swimmers will be eligible to the study, a population of 40 participants in total can be evaluated for this study purposes. Using previous studies comparing the rate number of respiratory infections for this specific population, elite swimmers under 12 weeks high intensity period before competitions 40% have a respiratory infection, with an alpha of 0,05 the power will be 35%.

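### Study II's regression model enters BMI in categories, discarding information that 40 swimmers from one team can ill spare

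*Protocol*

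**What the plan says.** For the swimmers (Study II), section 4.3.2 names the variables that may enter the regression model. The list opens with "gender, age, BMI (variable categorized), anthropometric changes" and ends with "asthma, bronchial hyper-responsiveness, airway inflammation presence and immunological mediators". BMI is the only variable marked as categorized. The elderly model (Study III), in the same section, lists BMI without that mark.

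The anthropometric part of section 4.2.3, headed for Studies II and IV, calculates BMI from measured weight and height and then states: "Individuals will be classified according to World Health Organization (WHO) classifications". The three classes are 18.5 to 24.9, 25.0 to 29.9, and 30.0 kg/m² or more. The protocol gives no other BMI grouping and does not say that these classes are the ones used in the model.

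Section 4.2.4 gives one sputum cut-off: "Sputum eosinophilia will be defined as a sputum differential of eosinophil count over 4" (per cent). That section is headed for Study III, but section 4.1.2 lists induced sputum among the swimmers' baseline tests, together with exhaled nitric oxide.

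On size, the sample size paragraph for the athletes says "a population of 40 participants in total can be evaluated for this study purposes" and "40% have a respiratory infection, with an alpha of 0,05 the power will be 35" (per cent).

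**The concern.** Grouping a continuous predictor treats everyone within a class as identical. The cost is highest when the cohort is small and alike and the cut-point lies in the tail. All three may hold here: there are 40 people, they come from one elite team, and the only cut-points on offer were made for the general population. A BMI effect that exists could then be missed, and an odds ratio that rests on a handful of swimmers in the upper class would be unstable.

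This is not a detail that the protocol leaves to a later analysis plan. The protocol itself fixes that BMI is categorized; only the cut-points are open.

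**Working it through.** **Inputs from the protocol.** 40 swimmers, 40% expected to be infected, stated power 35% at alpha 0.05. Expected infections: 0.40 × 40 = 16, leaving 24 uninfected.

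**The stated 35%.** It cannot be reproduced, because no comparator, exposure prevalence or effect size is given. It can only be back-solved:
- 20 v 20, two-sided, 40% against 65%: power 0.349.
- 20 v 20, two-sided, 40% against 16% or 18%: 0.39 or 0.33, so about 17% matches.
- 16 infected v 24 uninfected, standardized difference 0.5: 0.341.

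Nothing below depends on this figure.

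**Information kept by a two-class cut.** For a normal predictor with a linear effect, cut so that a fraction q lies above the cut-point z, the efficiency relative to the continuous term is E = φ(z)² / [q(1 − q)].

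| q (assumed) | z | φ(z) | E | 40 × E |
|---|---|---|---|---|
| 0.50 | 0 | 0.399 | 0.637 | 25.5 |
| 0.10 | 1.282 | 0.175 | 0.342 | 13.7 |
| 0.05 | 1.645 | 0.103 | 0.224 | 9.0 |

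The median split is the best two-class cut, so about 64% is the ceiling.

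**If the WHO cut at 25 is used.** The protocol gives no BMI distribution, so the range below is an assumption (normal, mean 21 to 23, SD 1.5 to 2.5).

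| Mean, SD | Share at 25 or more | Swimmers of 40 | E of the cut at 25 |
|---|---|---|---|
| 21, 1.5 | 0.004 | 0.2 | 0.03 |
| 22, 1.5 | 0.023 | 0.9 | 0.13 |
| 22, 2 | 0.067 | 2.7 | 0.27 |
| 22.5, 2 | 0.106 | 4.2 | 0.35 |
| 23, 2 | 0.159 | 6.3 | 0.44 |
| 23, 2.5 | 0.212 | 8.5 | 0.50 |

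The expected number of obese swimmers is about 0.1 or fewer in every row, so in practice the three classes reduce to a cut at 25.

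**Power, by simulation.** 40 swimmers, about 40% infected, 2,000 runs per setting. The continuous predictor is tested by t-test and the two-class version by Pearson chi-square, at the 5% level with no other covariates. The cut at +1.5 SD is the WHO cut of 25 when BMI is 22 ± 2.

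| Odds ratio per SD (assumed) | Continuous | Median cut | Cut at +1 SD | Cut at +1.5 SD |
|---|---|---|---|---|
| 1.5 | about 0.22 | 0.16 | 0.13 | 0.09 |
| 2 | about 0.50 | 0.38 | 0.27 | 0.17 |
| 2.5 | about 0.71 | 0.53 | 0.40 | 0.22 |

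The grouped version is weaker in every setting.

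**The case against.** The strongest reply is that this is one coding choice for one candidate among 17 in a data-driven, exploratory model. With about 16 expected infections there are 16/17 ≈ 0.9 events per listed candidate. That is the larger problem, and recoding BMI does not solve it. This stands, and it limits the weight of the point.

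Grouping may also have a purpose: section 4.3.2 plans a relative risk for each risk factor, which needs exposure groups. Section 4.3 provides t-tests or Mann-Whitney tests for continuous variables, and section 4.1.2 compares swimmers with and without infection, so continuous BMI can still be compared between those groups. Both points stand. They confine the loss to the regression model but do not justify grouping there.

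A reader might infer more than the text supports:
- **That Study II groups its continuous risk factors in general.** Only BMI is marked. Sleep quality and anxiety are listed without grouping, body fat is not said to be grouped, and anthropometric change is a separate, ungrouped candidate.
- **That airway inflammation is entered as eosinophils above 4%.** The model list says "bronchial hyper-responsiveness, airway inflammation presence and immunological mediators" and does not define presence. The cut-off stands in a section headed for Study III, and exhaled nitric oxide is also measured. The link is an inference.
- **That the WHO classes are the model's classes.** They are the only ones given, but the protocol does not make the connection. With another grouping, the sparse-class argument may fall away and the general cost of grouping remains.
- **That three classes waste a second degree of freedom.** This has little force if the obese class is empty, as expected here.

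**Conclusion.** The point holds for BMI in the Study II regression model. The protocol groups a continuous measurement without giving a reason, in a small and probably homogeneous cohort, and does not do so in its other model. Under normality and a linear effect, a two-class version keeps at most about 64% of the information, and about 34% or 22% if the upper class holds 10% or 5% of swimmers. Over the assumed BMI range, a cut at 25 keeps between 3% and 50%. The class fractions, the BMI range and the effect sizes are assumptions; the direction of the loss does not depend on them if the effect is close to linear.

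The same reasoning reaches airway inflammation only if its presence is defined by the 4% eosinophil cut-off. The efficiency figures should not be carried over to raw eosinophil percentages, which may be skewed. The point gives no explanation for the stated 35% power and no ground for changing the sleep or anxiety scores. It is a worthwhile refinement of an exploratory analysis, not a threat to the study.

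**What to change.** In the Study II variable list in section 4.3.2, replace the categorized BMI with BMI as a continuous term in kg/m², using one degree of freedom, with linearity checked on a plot. State that the WHO classes in section 4.2.3 serve to describe the sample and to form exposure groups for the relative risks.

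Define presence of airway inflammation in the same list. If it means the 4% sputum eosinophil cut-off, enter the eosinophil percentage as a continuous term instead, log-transformed if skewed, as section 4.3 already allows. The sleep and anxiety scores need no change.

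The cost is a change of analysis wording; no new data or measurements are needed. The downside is the assumption of a linear effect, which the plot can check.

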### **Methods:**

Study design: An observational study with validation methodology will be applied to evaluate respiratory infections; in prospective cohort study of 12 weeks a group of athletes under high competition levels, respiratory infections and potential risk factors accordingly to literature will be evaluated; an prospective case-control with a moderate- exercise program intervention will compare the impact in respiratory infections in elderly under exercise training or not; a randomized, placebo controlled cross-over trial will evaluate the impact of a high fat/high energy meal challenge in an acute exercise challenge; randomized clinical trial will be used to ascertain the impact of physical activity reduction in the immune function

Selection of participants: For questionnaire validation will be selected participants with respiratory infections; athletes will be selected from a high elite pre-competition level team; elderly will be selected from general population, namely from senior universities and nursing homes; asthma and obese participants will be selected from an university population sample

Sample Size: 281 patients will be chosen as target for evaluation in respiratory tract infections validation; 40 patients will be evaluated in total in swimmers illness-prone study trial; 40 participants will be selected to evaluate exercise program in the elderly; 30 participants, with a

equal number of obese, asthma, obese and asthma and a control will be allocated to the meal interventions (60 participants in total) and a target of 60 participants will be randomized to the physical inactivity intervention.

Measurements: Upper respiratory tract infections number, severity and quality of life impact, immune system markers, complete blood cell count, pro-inflammatory and anti-inflammatory mediators, namely cytokines, and metabolomic.

Main Outcomes: Respiratory Infection Risk in Susceptible Population, Immune markers parameter related with acute exercise and physical inactivity interventions (balance between pro-inflammatory and anti-inflammatory cytokines).

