Exercise and immune system changes are probably in relation with the subject susceptibility. Elderly are frequently recommended to perform physical activity and exercise due to its multiple positive effects on health-related problems[19] and it has been seen as a countermeasure to immune-senescence[20, 21]. It has been shown that the less physically active elderly have an increase on respiratory tract infections[22]. Most of the previous literature focuses on immune mediators response to exercise intervention in elderly, contradictory effects have been seen between cross-sectional and longitudinal studies as it was reported by a recent thorough literature review [21, 23]. This suggests that perhaps other markers should be evaluated, namely specifically patient related outcomes. Only one study performed in postmenopausal women evaluated disease as a main outcome after a 12 months moderate exercise intervention and reported a reduced incidence of common colds[24]. Further investigation is needed to evaluate the true impact of chronic regular exercise in restoring immune function and which factors can be effectively associated to potentiate it. Also, acute exercise might also have a deleterious effect and could limit the beginning of a regular physical activity in illness-prone subjects. This potential effect can be supported by the previously open window theory and immune changes related to them [13]. Acute exercise effect has seldom been studied in populations other than athletes or healthy physical active populations [12, 25, 26]. In Mills et al[27] study proposed that being physically fit is protective of inflammatory responses so the previously seen results might be more significant in sedentary and in persons with chronic inflammatory systemic diseases. Possibly, reducing the physical activity will be associated also with a decreased immune function response. This was previously demonstrated by recent studies of Pedersen group, where there was seen after a short reduction of physical activity a decrease in insulin sensitivity and cardiovascular fitness. Effect of this intervention on immune function has never been studied[28-30].

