#### **Participants**

Recruitment occurred from September until November 2010 through Exercise Health for the Elderly program, organized by The Research Centre in Physical Activity, Health and Leisure, at Faculty of Sport Sciences and Physical Education at the University of Porto, which receives patients from the Porto metropolitan area, Senior Universities from Porto and also nursing homes and daily care centers for the elderly in Northern region of Portugal. Participants were contacted by phone or personal contact at the universities or nursing homes. Intervention group participants belonged mainly from Porto metropolitan area, as they had the ability to travel to the training sessions that occurred at Faculty of Sport Sciences and Physical Education at the University of Porto. Control group were recruited from nursing rooms and daily care centers from Paredes de Coura, and all of those from Porto metropolitan area which were not able to participate in the intervention group by schedule incompatibilities. Participants were eligible if they had: over sixty years old, a medical report describing that they were physically able to practice aerobic and anaerobic exercise of moderate intensity and did not participated in previous physical exercise programs. Exclusion criteria included all patients with uncontrolled disease, namely hypertension, patients with cardiac or orthopedic prosthesis, patients with a psychological, familial or sociological problem that might compromise their compliance to the exercise program. Participants were provided with written information about the exercise training program and symptoms diary data collection. A total of 80 patients were recruited for

the study, 12 did not meet the eligibility criteria and 30 refused to participate, so 38 patients were selected. Participants were then assigned to the training group and control group accordingly to the availability and proximity to the exercise training group.

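### Study III's stated 30% power rests on 40 people per group, but 38 in total were assigned (about 12–22% power if split evenly), and the two assumed infection risks are attached to the wrong arms

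*Protocol*

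**What the plan says.** Section 4.3.2 explains that power was calculated because "infrastructure conditions only allowed a maximum sample of 40 persons in each group to be included". It then takes two infection risks from reference 24, a study in postmenopausal women. The risks are given twice, both times with the higher one on the exercise side: "having an infection during an moderate-exercise intervention, 48% had at least one episode of respiratory infections", and then, for the exercise group first, "48% change of having infection and 30% of having infections in the non-exercising group the power would be 30" per cent. Neither the test nor its sidedness is stated there. Section 4.3 allows either Pearson chi-square or Fisher's exact test for discrete outcomes.

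Three other places bear on this:

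- Summary, Sample Size: "40 participants will be selected to evaluate exercise program in the elderly". The Portuguese summary repeats this figure.
- Section 4.1.3, Participants, in the past tense: of 80 people, "12 did not meet the eligibility criteria and 30 refused to participate, so 38 patients were selected". They were then placed in the training or control group by availability and proximity. The size of each group is not given.
- Section 1, Rationale: reference 24 assessed disease "after a 12 months moderate exercise intervention and reported a reduced incidence of common colds[24]". The title of item 24 in the reference list gives the same direction.

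**The concern.** There are two separate faults in one short passage.

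First, the power figure belongs to a trial of up to 80 people. The Summary never planned that many, and section 4.1.3 shows they were not obtained. The protocol is dated 10 December 2012 and recruitment ran from September to November 2010, so the number 38 was available when the power sentence stood in this document. A reader who takes 30% at face value credits the trial with more sensitivity than it has.

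Second, the effect used for planning has exercisers infected more often than non-exercisers. That contradicts the protocol's own description of the cited study and the protective effect that motivates Study III. A reader cannot tell from section 4.3.2 which direction the trial was planned to detect.

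**Working it through.** **Inputs.** Risks 0.48 and 0.30, alpha 0.05 and 40 per group come from section 4.3.2. The total of 38 comes from section 4.1.3 (80 − 12 − 30 = 38). Two assumptions are needed because the document is silent: a two-sided test, and a 19:19 split.

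**Formula (normal approximation, n per group).** With d = 0.48 − 0.30 = 0.18 and pooled risk 0.39:

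- se0 = √(0.39 × 0.61 × 2/n)
- se1 = √((0.48 × 0.52 + 0.30 × 0.70)/n) = √(0.4596/n)
- power = Φ((d − c − 1.96 × se0)/se1), where c = 1/n with the continuity correction and c = 0 without it.

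For Fisher and Pearson, power was obtained by enumerating every pair of binomial outcomes and adding the probability of those with p ≤ 0.05.

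**Step 1: reproduce the stated 30% at 40 per group.** se0 = 0.1091, se1 = 0.1072.

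- Continuity-corrected: (0.18 − 0.025 − 0.2138)/0.1072 = −0.548, power 29.2%.
- Two-sided Fisher exact: 30.1%.
- Uncorrected pooled z: (0.18 − 0.2138)/0.1072 = −0.315, power 37.6%.
- Pearson, by enumeration: 38.6%.

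The stated 30% is therefore what Fisher's test or the continuity-corrected formula gives for 40 per group.

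**Step 2: the same calculation at 19 per group.** se0 = 0.1583, se1 = 0.1555.

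- Continuity-corrected: (0.18 − 0.0526 − 0.3102)/0.1555 = −1.175, power 12.0%.
- Uncorrected pooled z: (0.18 − 0.3102)/0.1555 = −0.837, power 20.1%.

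| Two-sided method | 40 per group | 20 per group (planned total 40) | 19 per group (actual total 38) |
|---|---|---|---|
| Fisher exact | 30.1% | 13.6% | 14.2% |
| Continuity-corrected z | 29.2% | 12.8% | 12.0% |
| Uncorrected pooled z | 37.6% | 21.0% | 20.1% |
| Pearson, enumerated | 38.6% | 21.0% | 22.3% |

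The enumerated tests rise slightly from 20 to 19 per group because the outcome is discrete.

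**Step 3: unequal splits of 38, Fisher, both directions.** 18:20 gives 16–17%; 24:14 gives 15–16%; 25:13 gives 15%; 28:10 gives 9–14%.

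**Step 4: scale.** By the uncorrected formula, 80% power for 48% v 30% needs about 115 per group; with the continuity correction, about 125.

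**Step 5: direction.** Section 4.3.2 has 48% with exercise and 30% without, citing reference 24. The Rationale and the reference title have fewer colds with exercise in that same reference. Both cannot be right. Exchanging the two risks leaves every two-sided figure in the table unchanged, because the groups are equal there; with unequal splits it moves power slightly (Step 3).

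**The case against.** **The 30% might come from the smaller sample.** Because 40 per group reproduces the figure, a reader might infer that nothing else does. That is not so: a one-sided uncorrected z-test gives 30.3% at 19 per group and 31.3% at 20 per group. A slip of 40 per group for 40 in total therefore cannot be ruled out. However, the text says 40 in each group and mentions no one-sided test, so 40 per group is the better reading. On either account the sentence needs correcting.

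**14% is not the one true value.** Test, sidedness and split are all open. Pearson gives 22% at 19:19, which is closer to the stated 30%. This stands, and it is why a range is given. Compared like with like, though, 38 people have roughly half the power of 80 on each method (14% v 30%, 22% v 39%).

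**The trial is openly underpowered.** The protocol concedes 30% and gives infrastructure as the reason. A null result would be inconclusive at 30% as it is at 14%. This also stands: the correction does not change how a null result should be read, only how weak the trial is said to be.

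**Target against achieved.** The Summary's 40 and the 38 in section 4.1.3 are a target and an outcome, and do not conflict. The conflict is with 40 per group.

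**Exercise as harmful.** A reader might infer from the risks that the planned hypothesis was harm. The Rationale says otherwise, so this is a labelling error. Nor do the documents show that the source reported exactly 30% with exercise and 48% without. They establish only its direction.

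**Conclusion.** The point holds. The power stated for Study III is for 40 people per group, which the trial neither planned in its Summary nor obtained. For the 38 people assigned, two-sided power to separate 48% from 30% is about 14% by Fisher's test, a method that reproduces the stated figure, and 12–22% across methods. This rests on an assumed 19:19 split and a two-sided 5% level; a 25:13 split gives about 15% by Fisher. Section 4.3.2 also plans a completed-protocol analysis, so any dropout would take the analysed number below 38.

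The arm labels contradict the protocol's own account of reference 24. This is an error in the stated direction of effect, with no numerical consequence for two-sided power when the groups are equal.

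The practical weight is moderate. Recruitment was over before the document's date, and the Milestones schedule the Study III analysis to end at month 18 of a project begun in September 2010. No enrolment decision depends on this. It is a statement that is wrong as written and flatters the trial.

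**What to change.** In section 4.3.2:

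- Replace the 40-per-group basis and the 30% with the 38 actually assigned, the actual number in each group, the named test and its sidedness, and the resulting power. If the split was 19:19 and the test two-sided, that is about 14% by Fisher (12–22% across methods).
- Check both infection risks against reference 24, then correct the arm labels to agree with the reduced incidence described in the Rationale.
- Add one sentence saying that a non-significant result in Study III is inconclusive and is not evidence of no effect. The relative risk with its 95% confidence interval is already planned there, so no new analysis is needed.
- Correct the study number in the same paragraph, which labels the elderly trial as II.

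The cost is text only. No design, data or analysis changes, and the stated power becomes less favourable.
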